**B.- Clinical Trial Design**

The study has been designed as a unicentric trial, to be carried out at the Hospital San Pedro, Logroño (La Rioja), Spain. Two groups will be studied, one will receive doxycycline (2 daily doses, 100 mg each) for 30 days, while the other will receive a placebo. Patients will be randomly assigned to one of the two arms following a 1:1 proportion (treatment:placebo). Masking will be done using a double blind technique, so neither the patient nor the doctor will know who is receiving doxycycline or placebo.

To complete the study, each patient will be asked to attend 4 visits to the clinic, as follow:

Visit 1. Clinical history data will be collected and the lesion will be properly diagnosed. If the patient meets the inclusion criteria and does not fulfil any of the exclusion criteria, he/she will be asked to participate in the trial and sign the informed consent form. Consenting patients will be given a code for identification throughout the study. A photograph of the affected eye (or both in bilateral lesions) will be taken. The Pharmacy of the Hospital will provide the patient with a capsule bottle (randomly assigned to his/her study code containing either doxycycline or placebo) and the proper instructions to take the medicine together with instructions for following visits and telephone numbers for potential adverse affects.

If a patient needs to be excluded or does not consent to be included in the study, he/she will be asked for informed consent to use cells from his/her resected pterygium for experiments on cell and molecular biology. All regular procedures will be followed with these patients.

Visit 2. This will happen 31 days alter the first visit. The degree of compliance will be evaluated and the number of capsules that were not taken for any reason will be recorded. A second photograph of the affected eye(s) will be taken to compare with that taken in the first visit. The ophthalmologist will again evaluate the lesion and, depending on the stage of this lesion, a decision will be taken to remove it or not, following the usual protocols set in place by the Ophthalmology Service. If the pterygium is removed, the tissue will be sent to the CIBIR for cellular and molecular analyses.

Visit 3. It will take place 6 months alter the second one. The doctor will recognize the patient and record his/her observations. Particular care will be devoted to annotate any recurrences.

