**C.-** **Objectives and outcome endpoints**

The main objective of the study is to reduce pterygium growth with a pharmacological treatment and reduce the Lumber of cases that need surgical resection of the lesion.

As secondary objectives we look forward to:

1.- Determine whether treatment with doxycycline reduce recurrence rates in patients whose pterygium was surgically removed.

2.- Investigate which genes and/or proteins change their expression following treatment of pterygium cells with doxycycline.

To accomplish these objectives, a photograph of the lesion(s) will be taken Turing the first visit. After 30 days of treatment, a second photography of the same area will be taken. The surface occupied by the lesion will be calculated in both photographs using an image analyzing software package. The main outcome will be the ratio between the surface occupied by the lesion in the second photograph divided by the size in the first one (growth rate).

As secondary outcomes, we will analyze the recurrence rate at 12 months after the intervention and the genomic/proteomic expression of the resected pterygium.

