**D.-** **Experimental drug**

Doxycycline is a long lasting tetracyclinic antibiotic derived from oxycycline, whose administration can be performed in a single daily dose. Doxycycline can be administered in different ways: orally, intravenously, subgingivally, and intragingivally. Following oral administration, 90-100 % doxycycline gets absorbed. Absorption is delayed when this drug is administered together with food or milk. In the same way, antiacids containing aluminium or iron salts significantly reduce absorption. Doxycycline crosses the placental barrier and is present in mothers´ milk. Most of the drug is excreted in the faeces, with very little being eliminated through the kidney. In the study doxycycline will be provided as 100 mg capsules, prepared by the Hospital pharmacy. Patients will take 2 capsules a day since the half life of this drug has been calculated at 16 hours (Archer et al. Treatment and prophylaxis of bacterial infections. In: Fauci et al. Editors. Harrison´s principles of internal medicine. 14th ed. New Cork:McGraw-Hill; 1998, pp 856-869). In addition, this dosis is optimal for significantly inhibiting the enzymes that degrade the extracellular matrix (Smith et al. Oral administration of doxycycline reduces collagenase and gelatinase activities in extracts of human osteoarthritic cartilage. J. Rheumatol. 25:532-535; 1998). Moreover, the use of this dosage for long periods of time, up to 30 months, produces very few and moderate adverse effects in patients (Brandt et al., Effects of doxycycline on progression of osteoarthritis. Results of a randomized, placebo-controlled, double blind trial. Arthritis Rheum. 52:2015-2025; 2005).

The control Group will receive identical capsules filled up with placebo (sugar pill).

Those patients excluded from the formal trial will be asked for permission (through informed consent) to use their excised pterygium tissue to establish cell cultures and perform additional cell and molecular biology studies.

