**F.-** **Statistical analysis**

The variables that will be statistically analyzed are, on the one hand, the growth or reduction of the surface occupied by the pterygium lesion after the treatment as compared with that before the treatment. In addition, the recurrence percentage in both arms and the expression of genes and proteins in pterygium cells either treated or not with doxycycline will be analyzed. First, normalcy of distribution and variance of the data will be checked. If data are distributed normally and present homoscedasticity, comparison between both groups will be performed with simple tools such as Student´s *t* test. Otherwise, non-parametric tests will be used. Differences will be considered statistically significant when *p*<0.05. All patients that return to their second visit will be included in the analysis (intention to treat analysis).

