**G.-** **Proposed time table**

Each specific patient will remain formally in the study for 13 months. In the first visit all pertinent data will be collected and he/she will be informed of the study´s dynamics. A photograph of the affected eye(s) will be taken in this first visit and the patient will receive a bottle with 60 capsules that need to be taken during the following 30 days. After this period, a second visit will take place where information regarding compliance with the treatment will be registered. In addition, a second photograph of the lesion(s) will be taken. After this, surgical resection of the pterygium will be performed in those patients that need it in accordance with the protocols of the Ophthalmology Service. All procedures will be done in the same way and by a maximum of 2 ophthalmologists. Two more visits will be scheduled at 6 and 12 months after the second one. In these sessions, the evolution of the lesion will be recorded and special attention will be paid to potential recurrences, in which cases the protocols of the Ophthalmology Service will be followed.

As it pertains to the whole study, 18 months seem to be enough to recruit the needed 98 patients. If we add the 13 months needed for the last patient to complete his/her follow-up, the study could close 31 months after it opens. We propose initiating the study on February 2009 and closing up on August 2011.

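### The by-arm expression comparison uses only lesions resected after treatment, so it is conditional on an event the drug is meant to change and is open to selection bias of unknown size

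*Protocol*

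**What the plan says.** Objective 2 in protocol section C is to "Investigate which genes and/or proteins change their expression following treatment of pterygium cells with doxycycline". The matching secondary outcome in the same section is "the genomic/proteomic expression of the resected pterygium".

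Tissue from trial patients reaches the laboratory by one route. Section B, visit 2, says that after the 30 days of capsules, "depending on the stage of this lesion, a decision will be taken to remove it or not", and then "If the pterygium is removed, the tissue will be sent to the CIBIR for cellular and molecular analyses". Section G repeats that "surgical resection of the pterygium will be performed in those patients that need it". No sampling before treatment, and none of lesions left in place, is described.

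Section C also makes it part of the main objective to reduce the number of "cases that need surgical resection of the lesion".

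Section F says that "the expression of genes and proteins in pterygium cells either treated or not with doxycycline will be analyzed", alongside lesion surface and recurrence, by a t test or a non-parametric test. It does not mention that only some patients supply tissue.

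Sections D and E add a second source outside the randomised comparison: patients excluded from the trial are asked for permission to "use their excised pterygium tissue to establish cell cultures and perform additional cell and molecular biology studies".

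**The concern.** Randomisation makes the two arms comparable as randomised. It does not make comparable the subsets that go on to surgery, because surgery is decided after 30 days of study drug and on a feature of the lesion that the drug is intended to alter. If doxycycline works as hoped, some treated lesions will no longer need removal and will supply no tissue; a lesion that disappears cannot supply any. The doxycycline samples then come on average from lesions that shrank less. The placebo samples are selected too, but by a different amount.

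A difference in expression between the two sets of tissue, or its absence, could therefore reflect who was operated on as well as what the drug did. The more the drug succeeds in sparing surgery, the stronger the selection. At stake is the mechanistic conclusion of a secondary outcome; the primary endpoint and the sample size are not affected.

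**Working it through.** **Inputs from the protocol (section E).** Mean reduction 5% on placebo and 15% on doxycycline, SD 15% in both, two-sided 5% level, 49 per arm.

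**The plan's own figure.** The normal formula is n = 2(z₁ + z₂)²(SD/difference)². At 90% power, 2 × (1.960 + 1.282)² × (15/10)² = 47.3, so 48; the exact t test gives 48.3, so 49. At 80% power the two methods give 36 and 37. The protocol states 49 and 35, so its figures reproduce to within two patients and the inputs can be used.

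**Not in the protocol, so assumed.** The share resected per arm, the rule that turns stage into a decision, and the link between expression and shrinkage.

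**Assumption A: a lesion is resected if it shrank by less than a cut-off c.** The mean shrinkage of resected lesions is m − 15·φ(b)/Φ(b), with b = (c − m)/15, and the share resected is Φ(b). Worked for c = 15:

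- Doxycycline: b = 0, mean 15 − 15 × 0.3989/0.5 = 3.03, share 50%.
- Placebo: b = 0.667, mean 5 − 15 × 0.3194/0.7475 = −1.41, share 75%.
- Contrast among resected lesions: 3.03 − (−1.41) = 4.44, against 10 in all randomised patients.

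A simulation of one million patients per arm agrees (4.43) and gives the table below. The last two columns take an expression effect of 10/15 = 0.67 SD. They show the percentage of that effect that remains and, in brackets, the power with the resected samples alone, for a correlation of 1 or 0.5 between expression and shrinkage.

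| Cut-off | Resected, placebo / doxycycline | Contrast left of 10 points | Correlation 1 | Correlation 0.5 |
|---|---|---|---|---|
| 40% | 99% / 95% | 8.8 | 88% (87%) | 94% (88%) |
| 30% | 95% / 84% | 7.2 | 72% (76%) | 87% (80%) |
| 20% | 84% / 63% | 5.3 | 53% (54%) | 76% (62%) |
| 15% | 75% / 50% | 4.4 | 44% (41%) | 72% (51%) |
| 10% | 63% / 37% | 3.6 | 36% (28%) | 68% (39%) |
| 5% | 50% / 25% | 3.0 | 30% (19%) | 65% (28%) |

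**Assumption B: a lesion is resected if its remaining size exceeds a threshold,** with an assumed baseline coefficient of variation of 30%. This is closer to a decision on stage, because baseline size also counts.

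| Resected, placebo / doxycycline | Contrast left of 10 points | Mean shrinkage on doxycycline, resected / not resected |
|---|---|---|
| 95% / 92% | 9.6 | 14.1% / 25.9% |
| 75% / 65% | 8.4 | 10.8% / 22.7% |
| 50% / 37% | 7.5 | 6.9% / 19.8% |
| 25% / 15% | 6.7 | 2.0% / 17.3% |

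**Direction.** Under A with zero correlation, the expression effect is kept in full and only samples are lost (power 62% at the 10% cut-off, from 49 × 0.63 ≈ 31 placebo and 49 × 0.37 ≈ 18 doxycycline lesions). With an inverse correlation of −0.5 or −1 and cut-offs of 20% to 5%, the effect is overstated 1.2 to 1.7 times.

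**The case against.** The strongest reply is that the selection may matter little, and that objective 2 may not depend on trial tissue at all.

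- **Many may be operated on anyway.** Section E admits patients with symptoms, and section H describes surgery as put off by four weeks. If nearly all are resected, the loss is small: 8.8 or 9.6 of 10 points in the mildest scenarios. This stands as a limit on size, but the protocol does not state the share, and a near-universal resection rate would run against its own aim of fewer operations.
- **Cells may be treated in the laboratory.** Objective 2 and section F speak of cells treated or not with doxycycline, which can be read as a laboratory experiment. This stands: a reader might infer that expression is studied in resected trial lesions alone, and the text does not settle that. The declared outcome in section C is nonetheless resected tissue.
- **It could be left to the SAP.** Detailed handling could be. But the protocol itself fixes the outcome, the tissue source and the type of test, and these together create the problem.

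A reader might also infer that the drug's effect on expression will be understated or missed. That needs expression change to go with shrinkage. The protocol suggests a mechanism through inhibition of matrix-degrading enzymes but establishes no such link.

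Nor does the text support calling the doxycycline tissue donors non-responders. The rule is stage, which also reflects baseline size, and in several scenarios most doxycycline patients supply tissue.

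**Conclusion.** The concern holds as a risk of selection bias. Followed as written, the by-arm tissue comparison is conditional on resection, which treatment is meant to change, and so does not estimate the effect of doxycycline in the randomised patients.

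The size cannot be fixed from the protocol. On its own means and SD, the contrast in shrinkage falls by 12% to 70% under an assumed shrinkage cut-off of 40% down to 5%, and by 4% to 33% under an assumed remaining-size rule. The upper part of the first range should not be taken as the expected loss, because a rule on shrinkage alone is not the protocol's stage rule. How far any of this carries over to expression depends on a correlation the documents do not give.

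It might seem that the cultures in sections D and E already offer a within-donor comparison with and without drug. They do not: cultures are foreseen only from excluded patients, adding doxycycline to them is not mentioned, and such an experiment would answer a different question from 30 days of oral treatment.

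**What to change.** In sections C and F:

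1. State that the by-arm comparison of resected tissue is exploratory, conditional on resection, and not an estimate of the randomised drug effect.
2. Report the number and share of lesions resected in each arm.
3. Show baseline area and visit 2 area ratio for resected and unresected lesions by arm, and put each contributor's area ratio beside the expression data.
4. State whether objective 2 is answered from trial tissue or from laboratory-treated cells.

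The cost is wording and one descriptive table. The areas are already measured for the main outcome, and no visit, sample or surgical decision changes. The downside is that the patient-tissue result can no longer be presented as the drug's effect.

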**D.-** **Experimental drug**

Doxycycline is a long lasting tetracyclinic antibiotic derived from oxycycline, whose administration can be performed in a single daily dose. Doxycycline can be administered in different ways: orally, intravenously, subgingivally, and intragingivally. Following oral administration, 90-100 % doxycycline gets absorbed. Absorption is delayed when this drug is administered together with food or milk. In the same way, antiacids containing aluminium or iron salts significantly reduce absorption. Doxycycline crosses the placental barrier and is present in mothers´ milk. Most of the drug is excreted in the faeces, with very little being eliminated through the kidney. In the study doxycycline will be provided as 100 mg capsules, prepared by the Hospital pharmacy. Patients will take 2 capsules a day since the half life of this drug has been calculated at 16 hours (Archer et al. Treatment and prophylaxis of bacterial infections. In: Fauci et al. Editors. Harrison´s principles of internal medicine. 14th ed. New Cork:McGraw-Hill; 1998, pp 856-869). In addition, this dosis is optimal for significantly inhibiting the enzymes that degrade the extracellular matrix (Smith et al. Oral administration of doxycycline reduces collagenase and gelatinase activities in extracts of human osteoarthritic cartilage. J. Rheumatol. 25:532-535; 1998). Moreover, the use of this dosage for long periods of time, up to 30 months, produces very few and moderate adverse effects in patients (Brandt et al., Effects of doxycycline on progression of osteoarthritis. Results of a randomized, placebo-controlled, double blind trial. Arthritis Rheum. 52:2015-2025; 2005).

The control Group will receive identical capsules filled up with placebo (sugar pill).

Those patients excluded from the formal trial will be asked for permission (through informed consent) to use their excised pterygium tissue to establish cell cultures and perform additional cell and molecular biology studies.

**E.-** **Patients**

**Total Lumber of patients**

There are 2 ways of calculating sample size to reach statistical significance in a clinical trial. The first one is a qualitative strategy where each patient is classified as a success or a failure to the treatment depending on whether their lesion size shrinks below a predetermined value (threshold). This allows a comparison between groups using a bilateral 2 for 2 independent samples. From the study of the disease we know that untreated pterygia keeps growing or maintains its size, but never tends to spontaneously reduce its size, so we can assume that the proportion of the placebo-treated group is asymptotically 0.0%. Depending of the power and the established threshold, the number of patients for each group are the following:

| **Power** | **Treshold at 25%** | **Treshold at 50%** | **Treshold at 75%** | **Treshold at 100%** |
| --- | --- | --- | --- | --- |
| 80% | 27* | 11 | 6 | 1 |
| 90% | 35 | 14 | 7 | 2 |

* Numbers indicate sample size on each group.

Secondly, we can also use a quantitative strategy where each patient receives a numeric value representing the percentage reduction (or growth) of his/her pterygium due to treatment. In this case, to detect significant differences in the null hypothesis contrast Ho:1=2 we will use a bilateral Student´s *t* test for 2 independent samples. If we assume that the mean reduction of the lesion in the placebo group is 5 % and in the doxycycline-treated group is 15 %, and that the standard deviation in both groups is a maximum of 15%, for a significance levels of 5%, the number of subjects is as follows:

| **Power** | **Number of patients per group** |
| --- | --- |
| 80% | 35 |
| 90% | 49 |

Since it is difficult to forecast the expected response, we have decided to follow the most stringent conditions and 98 patients will be recruited (49 treated with doxycycline and 49 treated with placebo). This sample size will allow to detect significant differences of 10% or higher in the diminution of pterygium size between the treated and the placebo groups. Besides, this number of patients will allow the qualitative analysis previously explained.

Recruitment will be performed among patients attending the Ophthalmology Service of the Hospital. Currently, 4 to 8 pterygium patients visit the Hospital every month.

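### The responder sample-size table uses lesion-shrinkage thresholds as responder proportions against a 0% placebo rate, so the statement that 98 patients allow the responder analysis does not hold under the protocol's own means and SD

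*Protocol*

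**What the plan says.** Section E (Patients), under the total number of patients, gives two calculations.

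- **Qualitative.** Each patient is a success or a failure, "depending on whether their lesion size shrinks below a predetermined value (threshold"). The arms are compared with a two-sided two-sample test, evidently chi-square with the symbol lost in extraction. Untreated lesions are said to grow or stay the same size but "never tends to spontaneously reduce its size", and from this "we can assume that the proportion of the placebo-treated group is asymptotically 0.0"%. The table gives patients per group at thresholds of 25, 50, 75 and 100%: 27, 11, 6 and 1 for 80% power, and 35, 14, 7 and 2 for 90%. The section does not say what share of doxycycline patients is expected to pass any threshold.
- **Quantitative.** A two-sided t test, assuming "the mean reduction of the lesion in the placebo group is 5 % and in the doxycycline-treated group is 15"%, with an SD of at most 15% in both groups. This gives 35 or 49 per group.

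The protocol takes 49 per group as the most stringent case and closes with "Besides, this number of patients will allow the qualitative analysis previously explained".

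Section C makes the ratio of lesion surface after treatment to that before the main outcome. Section F lists change in surface, recurrence, and gene and protein expression as the variables to analyse. Neither section names a responder endpoint.

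**The concern.** A threshold on lesion size and the proportion of patients who pass it are different quantities. A sample size for comparing two proportions needs the second, and the protocol states only the first. The two calculations also disagree about placebo: in one, untreated lesions do not tend to shrink; in the other, they shrink by 5% on average.

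A reader of the closing statement would conclude that 49 per arm exceeds every number in the table and therefore gives better than 90% power at any listed threshold. If that is wrong, a non-significant responder comparison could be taken as evidence against an effect when the comparison had little chance of showing one.

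**Working it through.** **Inputs**, all from section E: doxycycline mean reduction 15%, placebo 5%, SD at most 15%, 49 per arm, two-sided tests. The 5% significance level is stated for the t test and is assumed to apply to the table as well. Thresholds are read as percentage reduction from baseline.

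**1. Reproducing the table.** The pooled formula without continuity correction, with p the doxycycline proportion, 0 on placebo and p̄ = p/2, is

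n per arm = [1.960·√(2p̄(1−p̄)) + z_β·√(p(1−p))]² / p²

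For p = 0.25 and 80% power: [1.960·0.4677 + 0.8416·0.4330]² / 0.0625 = 26.3, which rounds up to 27.

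| Value entered as p | 80%: computed | 80%: printed | 90%: computed | 90%: printed |
|---|---|---|---|---|
| 25% | 26.3 | 27 | 34.7 | 35 |
| 50% | 10.5 | 11 | 13.6 | 14 |
| 75% | 5.2 | 6 | 6.4 | 7 |
| 100% | 1.92 | 1 | 1.92 | 2 |

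Rounded up, seven of the eight cells match. One-sided, continuity-corrected, unpooled and arcsine versions do not reproduce the table. The column headings were therefore used as responder proportions. The remaining cell should be 2. With one patient per arm and complete separation, the chi-square statistic is 2.0, below the critical 3.84; with two per arm it is 4.0.

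**2. The t-test calculation.** 2·(1.960 + 0.8416)²·15²/10² = 35.3 for 80% power, and 2·(1.960 + 1.2816)²·15²/10² = 47.3 for 90%. The exact t calculation needs 37 and 49. The printed figures are 35 and 49. At 49 per arm the exact power is about 90%, so the basis for 98 patients stands.

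**3. Responder rates implied by the quantitative assumptions.** With normal percentage reduction, P(reduction > c) = 1 − Φ((c − mean)/SD).

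- Any shrinkage on placebo: 1 − Φ(−5/15) = 63%.
- c = 25%, SD 15: doxycycline 1 − Φ(0.667) = 25.2%; placebo 1 − Φ(1.333) = 9.1%.
- c = 50%, SD 15: doxycycline 1 − Φ(2.333) = 0.98%; placebo 1 − Φ(3) = 0.13%.
- c = 75% or 100%: practically no responders in either arm.

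**4. Power at 49 per arm.** This sums the two binomial distributions over all outcomes in which the uncorrected two-sided chi-square test is significant at 5%.

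| Cut-off | SD | Doxycycline | Placebo | Power |
|---|---|---|---|---|
| 25% | 15 | 25.2% | 9.1% | 59% |
| 25% | 12.5 | 21.2% | 5.5% | 68% |
| 25% | 10 | 15.9% | 2.3% | 74% |
| 25% | 7.5 | 9.1% | 0.4% | 60% |
| 25% | 5 | 2.3% | 0.0% | 3% |
| 50% | 15 | 0.98% | 0.13% | 0.1% |

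At 50% and above, power is close to zero for every SD tried. At the 25% cut-off with SD 15, the pooled formula would need 85 per arm for 80% power and 113 for 90%.

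**5. Which error matters where.** At 25% the implied doxycycline rate happens to be 25.2%, so the shortfall comes from the placebo rate: with placebo at 0%, exact power exceeds 99%. At 50% the shortfall comes from treating the threshold as a proportion: with placebo set to 0%, power is still about 0.1%.

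**The case against.** The protocol presents the two calculations as alternatives because the response is hard to forecast, and it calls the quantitative one the most stringent. On the table's own premise of 25% responders against 0%, 49 exceeds 35 and exact chi-square power is 99.9%. The claim fails only when the second calculation's inputs are carried into the first. That is a fair description, but it does not rescue the statement. Both calculations describe the same two arms of the same trial, and one cannot assume an average placebo shrinkage of 5% while the other sets placebo success to zero on the ground that lesions do not tend to shrink. The mislabelled columns and the 100% cell are wrong without any appeal to the quantitative inputs.

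It is also true that the power figures assume normality and that 15% is a maximum SD. With smaller SDs some untabulated cut-offs do well: a 10% cut-off gives 76% at SD 15, 89% at SD 12.5 and 98% at SD 10. So it would be wrong to say that no responder analysis could be adequately powered. The shortfall concerns the thresholds that the protocol lists.

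Three stronger readings are tempting and are not supported:

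- A reader might infer that the trial is too small. It is not on this ground: the t test set the sample size.
- A reader might infer that a threshold will be picked from four after seeing the data, inflating the error rate. The protocol calls the threshold predetermined, the columns are planning scenarios, and the choice of one cut-off may sit in an analysis plan that is not shown.
- A reader might quote the lower power of Fisher's test (46% at the 25% cut-off with SD 15). The protocol does not name that test.

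**Conclusion.** The point holds as an error in the sample-size justification, confined to the responder calculation. The columns are mislabelled, one cell is 1 where the formula gives 2, and the placebo assumptions of the two calculations conflict. Given normal percentage reduction with means of 15% and 5%, no tabulated threshold reaches 80% power at 49 per arm for any SD tried from 5 to 15. Power is 59% at a 25% reduction with SD 15, at most about 74%, and essentially nil at 50% or more.

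The main outcome, its t test and the total of 98 are untouched, and the protocol lists no responder endpoint, so it is not established that this comparison will be run. This is a correction of stated figures and of one sentence, and it does not threaten the trial's main conclusion.

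**What to change.** In section E of the protocol:

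1. Relabel the table columns as the assumed responder proportion in the doxycycline arm.
2. Delete the 100% column, or correct its 80% entry from 1 to 2.
3. Use one placebo assumption in both calculations.
4. Replace the closing sentence with a conditional one, for example: if percentage reduction is normal with means of 15% and 5%, 49 patients per arm give about 59% power (chi-square, two-sided 5%) to compare the proportions with a reduction of more than 25% when the SD is 15%, and between about 3% and 74% for the SDs examined from 5% to 15%; any responder analysis is supportive.

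The cost is wording and restated figures. The number of patients, the procedures and the primary analysis do not change. The downside is a less favourable stated power for a supportive analysis.
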